**Background**

There are some problems such as platelets aggregation, increase of platelets activation, and functional disorder leading to thrombosis formation or bleeding during intraoperative and postoperative periods in coronary artery bypass surgeries. Because arterial thrombosis formation can cause serious outcome, some studies investigated various factors to prevent platelet aggregation and to inhibit increase of coagulation of blood.

Previous studies suggested that abnormality of platelet function increased at postoperative period compared to preoperative period in cases which CPB was used in the operation. Therefore, there was a hypothesis that abnormality of platelet function caused by CPB would lesser develop in off-pump CABG compared to CABG. Bendar et al. presented that changes of platelet function by evaluating increase of p-selectin in patients who received OPCAB or CABG. They reported that increase of p-selectin as a platelet activation marker was highest at 2 days after operation in patients who received OPCAB. Lo et al. reported that platelet activation in terms of coagulation was maximized at immediate postoperative period in CABG, and between 20 – 96 hours after operation in OPCAB. There are some methodologies in evaluating platelet activation, that is, not only p-selectin but also flow cytometry by which antigen on the surface of platelet can be estimated. The most dominant platelet activation markers are p-selectin, PAC-1, CD 63. They can be used to evaluate blood disorders or responses to anticoagulants.

Aspirin was a most used anticoagulant in patients who received cardiac surgeries. It is well known that aspirin decrease platelet function and increase bleeding tendency in CPB. However, there has been any strong evidence supporting that aspirin administration lead to increase of postoperative bleeding.

There are various opinions on the perioperative use of aspirin for OPCAB or CABG. The Society of Thoracic Surgeons recommends stop of aspirin use 3 days before operation to minimize complications concerned with blood transfusion. American Society of Chest Physicians recommended continuous use of aspirin even at operation day. The American College of Cardiology and American Heart Association recommended stop of aspirin use 7-10 days before OPCAB or CABG. Jacob et al. reported that there was no difference between late discontinuation (stop 4 days before surgery) and early discontinuation (stop 7-10 days before surgery) on the perioperative complications.

Bednar et al. investigated the effect of aspirin administration at immediate postoperative periods on the level of Thromboxane B2 in patient who did not receive preoperative aspirin for CABG. The study reported that thromboxane B2 decreased significantly by postoperative aspirin administration. This study helped many physicians make a strategy of anticoagulants use in CABG.

Rally et al. presented that the model of most strong acute inflammation in human could be explained with coronary artery bypass surgery. They showed outbreak of expression of a gene influencing platelet at 3-6 days after surgery which could increase risk of myocardiac infarction. They evaluated 45 genes. GpIIb, GpIIIa, and Cox-1 gene expression did significantly increase by 3 times compared with baseline in all 11 subjects in the study. If any mRNA and protein which have a great role in platelet aggregation would increase due to CABG, this could be an important factor cause increase of thrombosis.

Because previous studies did not control preoperative use of anticoagulants, they could not reveal the effect of preoperative aspirin use on gene expression which influence platelet aggregation or platelet activation. There were numerous studies about co-effect of antiplatelet agents and anticoagulants on the activity of platelet. However, there has been no consensus about preoperative use of them. Therefore, strategies of perioperative use of them are various according to centers. Therefore, a study on the effect of preoperative low dose aspirin use on the mRNA which have a great role on platelet activation and platelet aggregation ant protein expression by it should be needed.

**Purpose of study and Hypothesis**

**Purpose**

The purpose of this study is to evaluate the difference between mRNA estimated at preoperative periods and 3 days after operation in patients who received continuously low dose (100 mg) of aspirin until operating day and in patients who stopped aspirin 4 days before surgery. .

**Hypothesis**

Our hypothesis is that increase of mRNA at 3 days after surgery compared with preoperative value in patients who stopped aspirin 4 days before surgery will not be higher than it in patients who continue aspirin until operating day.

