**Number of subjects**

Reilly reported that outbreak of gene concerned with platelet which could increase risk of MI occurred at 3-6 days after operation in patients who received continuously aspirin until operating day before coronary artery bypass surgery. In the study, GPIIb, GpIIIa, COX-1 gene expression increased by 3 times in all of 11 patients compared to baseline. For OPCAB, there was no data on GpIIb, GpIIIa, COX-1 gene expression. Therefore, 20 subjects are needed for each group, that is, total of 40 subjects are needed for this study. Considering the loss rate of 20%, total of 48 subjects will be needed.

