**Clinical evaluation lists**

- volume of intraoperative bleeding

- volume of postoperative bleeding

- postoperative clinical outcomes : MACE (MI, stroke, coma, arrest), renal failure, re-admission

Primary Outcomes

Increase (%) of GPIIb mRNA at 96 h postoperative time point (T6) compared to baseline (before initiation of surgery, T1)

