**Statistical analyses**

Statistical analyses will be performed with intention-to-treat.

If data will be normal distributed, we will use student t-test or Chi square test. Otherwise, Mann-Whitney test or Fisher’s exact test will be used.

For the primary outcome, increase of GPIIb mRNA, independent t-test will be used.

For the evaluation discrepancy of platelet mRNA expression by aspirin effect between two groups at each time points, we will use the generalized estimating equation/general linear model. P-value < 0.05 will be considered to be significant.

Repeated-measures analysis and Bonferroni correction will be used for adequate analysis between groups.

Data will be presented as mean ± Standard deviation, median [interquartile range], and number of patients (%). All statistical analyses will be performed with IBM SPSS Statistics software (version 21, SPSS Inc., IBM Corporation, USA).

References

1. Bernard Lo, Rob Fijnheer, Domenico Castigliego, Cornelius Borst, Cor J. Kalkman, Arno P. Nierich, Activation of hemostasis after coronary artery bypass grafting with or without cardiopulmonary bypass. Anesth Analg 2004; 99: 634-40

2. Alessandro Parolari, Luciana Mussoni, Marta Frigerio, Moreno Naliato et al., The role of tissue factor and P-selectin in the procoagulant response that occurs in the first month after on-pump and off-pump coronary artery bypass grafting. The journal of thoracic and cardiovascular surgery 2005; 130(6): 1561-1566

3. Raymond Cartier, Current trends and technique in OPCAB surgery. J Card Surg 2003; 18: 32-46

4. Frantisek Bendar, Pavel Osmancik, Tomas Vanek, Heidi Mocikova, Martin Jares, Zbynek Straka, Petr Widmsky , Platelet activity and aspirin efficacy after off-pump compared with on-pump coronary artery bypass surgery: results from the prospective randomized trial PRAGUE 11-Coronary Artery Bypass and Reactivity of Thrombocytes (CABARET). The journal of thoracic and cardiovascular surgery 2008; 136(4): 1054-1060

5. Robert Poston, Junyan Gu, James Brown, James Gammie, Charles White, Jeffrey Manchio, Richard N. Pierson et al., Hypercoagulability affecting early vein graft patency dose not exist after off-pump coronary artery bypass. J of cardiothoracic and vascular anesthesia 2005; 19(1): 11-18

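### The hypothesis says that stopping aspirin is no worse, but the planned t-test looks for a difference, so similar arms could not support it and an inconclusive result could be misread as support

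*Protocol*

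**What the plan says.** Three statements in the protocol bear on this point.

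- **Hypothesis.** The mRNA increase "in patients who stopped aspirin 4 days before surgery will not be higher than it in patients who continue aspirin until operating day". The claim is one-sided: stopping does no worse than continuing.
- **Purpose.** "The purpose of this study is to evaluate the difference between mRNA estimated at preoperative periods and 3 days after operation" in the two aspirin groups. This is the language of a difference.
- **Statistical analyses.** "For the primary outcome, increase of GPIIb mRNA, independent t-test will be used", and "P-value < 0.05 will be considered to be significant". The analysis is by intention-to-treat.

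The protocol states no margin, no shifted null hypothesis, no confidence-limit rule, and nothing on which result would count as support for the hypothesis. The Number of subjects section says "Therefore, 20 subjects are needed for each group, that is, total of 40 subjects are needed for this study" and raises the total to 48 for loss. It gives no between-group difference, SD, power or sidedness. Its only quantitative basis is a within-patient rise in a cited study, where "GPIIb, GpIIIa, COX-1 gene expression increased by 3 times in all of 11 patients compared to baseline".

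**The concern.** An ordinary t-test takes equality of the two means as its null hypothesis and can only reject equality or fail to reject it. Failing to reject does not show that the increase after stopping is no higher. If the arms are truly similar, which the hypothesis allows, failing to reject is the likely outcome.

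The hypothesis and the test that is meant to address it therefore do not match. A small or noisy trial is more likely to give P≥0.05, so weak data would tend to look like agreement with the hypothesis. The protocol's Background says there is no consensus on preoperative antiplatelet and anticoagulant use and links raised platelet mRNA to thrombosis. An unsupported statement that the rise is no higher after stopping would feed directly into that debate.

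**Working it through.** **1. The plan's own figure.** The step from 40 to 48 is 40 × 1.2 = 48. The 20 per group cannot be reproduced, because no between-group effect, SD, power or sidedness is given. Solving backwards with the normal approximation (two-sided 0.05, 80% power), 20 per group corresponds to a difference of (1.960 + 0.842) × √(2/20) = 0.886 SD. That value is not in the protocol, and nothing there shows that the trial was sized for a no-worse conclusion.

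**2. What each result of the planned test could say about the hypothesis.**

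| Result of the t-test | Bearing on the hypothesis |
|---|---|
| Increase significantly higher after stopping | Contradicts it |
| Increase significantly lower after stopping | Supports it, but is a stronger claim than the one stated |
| P≥0.05 | Neither, without a margin |

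With no true difference, a two-sided 5% test gives the third row in 95% of trials and the second in 2.5% (0.05/2).

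**3. Inputs for the illustration.** From the protocol: 20 per group (Number of subjects), 24 per group as enrolled (Study protocol), 1:1 allocation, alpha 0.05. Assumed: SD = 1, so that differences are in SD units; true excesses of 0.5 and 0.8 SD; a two-sided test, with one-sided 5% as a variant.

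**4. Precision.** Half-width of the 95% confidence interval = t(0.975, 2n−2) × √(2/n).

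- n = 20: 2.024 × 0.3162 = 0.64 SD
- n = 24: 2.013 × 0.2887 = 0.58 SD

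An observed difference of exactly zero would still be compatible with an increase about 0.6 SD higher after stopping.

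**5. Chance that a true excess is non-significant.** Noncentral t with 2n−2 degrees of freedom and noncentrality d × √(n/2). For d = 0.5 this is 1.581 (n = 20) and 1.732 (n = 24); for d = 0.8 it is 2.530 and 2.771.

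| True excess after stopping | n per arm | Two-sided 0.05 | One-sided 0.05 |
|---|---|---|---|
| 0.5 SD | 20 | 66% | 54% |
| 0.5 SD | 24 | 60% | 48% |
| 0.8 SD | 20 | 31% | 20% |
| 0.8 SD | 24 | 23% | 14% |

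**6. What the planned size could support as a non-inferiority test.** At one-sided 2.5%, 80% power and no true difference, the margin that can be tested is 0.91 SD (n = 20) or 0.83 SD (n = 24) by exact t. The normal approximation gives 2.802 × 0.3162 = 0.89 and 2.802 × 0.2887 = 0.81. For a margin of 0.5 SD, exact power is 34% (n = 20) or 40% (n = 24), and the size needed is 2 × (2.802/0.5)² = 62.8, so 63 per group.

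**The case against.** The strongest reply is that this is a difference trial with one loosely worded sentence. The Purpose section and the t-test agree with each other, the words superiority and non-inferiority appear nowhere, and only the Hypothesis section points the other way. That is a fair reading. It determines which repair is best, but it leaves one of the protocol's central statements in conflict with the other two.

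A reader might infer two stronger things, and the protocol supports neither. One is that an inconclusive trial *would* be taken as proof that stopping is no worse. The protocol says only when a result counts as significant and is silent on how P≥0.05 will be interpreted, so the most that can be said is that it could be misread. The other is that a non-significant result is the only one that could confirm the hypothesis. A significantly lower increase after stopping would also support it, and validly.

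It can also be said that decision rules are often left to the SAP, which is not at hand. That would excuse missing detail. Here the hypothesis and the primary test are both already fixed in the protocol, and they do not fit together.

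Finally, the percentages depend on assumed SD units, sidedness and the number analysed. That stands, which is why ranges are shown. Across the cases shown, a true excess of 0.5 SD goes undetected in roughly half to two thirds of trials.

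**Conclusion.** The point holds as a mismatch between stated elements: a no-worse hypothesis, a purpose framed as a difference, and a test of equality without a margin. If the arms are similar, the planned test cannot turn that into evidence for the hypothesis. Only a significantly lower increase after stopping would support it validly.

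Under the assumptions above (SD units, two-sided test, 20 or 24 analysed per arm), a true excess of 0.5 SD would be non-significant in 66% or 60% of trials, and one of 0.8 SD in 31% or 23%. The one-sided variant lowers these to 54% or 48%, and 20% or 14%. The mismatch itself does not depend on any of these figures.

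This should be fixed. The recommended repair leaves the test and the sample size as they are, and the protocol does not itself commit to the wrong interpretation.

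**What to change.** **Recommended.** Reword the Hypothesis section as a difference hypothesis, in line with the Purpose section and the t-test: the increase in GPIIb mRNA differs between the continuation and discontinuation groups. In Statistical analyses, add that the between-group difference will be reported with its 95% confidence interval, and that P≥0.05 will not be interpreted as showing that the increase after stopping is no higher. This costs a few sentences and no patients; the conclusion allowed after a null result becomes more modest.

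**If the sponsor keeps the no-worse claim**, the plan needs:

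- a margin that is justified and fixed in advance;
- a rule that the claim is made only if the upper limit of the two-sided 95% confidence interval for discontinuation minus continuation lies below that margin;
- a per-protocol analysis beside the intention-to-treat analysis;
- a plain statement that 20 to 24 per arm gives 80% power (one-sided 2.5%, no true difference) only for a margin of about 0.91 to 0.83 SD.

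This route is not a wording-only change. A tighter margin needs more patients, for example 63 per group for 0.5 SD under the same assumptions.

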**Subject**

Patients receiving an elective OPCAB

**Expected study period**

12 months from IRB’s approval

**Inclusion criteria**

Adult patients more than 20 years old

Patient receiving an elective OPCAB, which is a first cardiac surgery to the patient

**Exclusion criteria**

Previous hematologic disease

Disorders of coagulation

Preoperative Plt. count < 100,000.

Preoperative PT INR > 1.2

Preoperative antithrombin III < 80% or 120%

Fibrinogen < 2g/L or 6g/L

Emergent operation

Reoperation of OPCAB

Combined operation with valvular surgery or aortic aneurysmal surgery

Hepatic disease

Renal disease

Recent MI within 12 months

Recent unstable angina within 10 days

Recent PCI history within 30 days

Implantation of Bare metal stent within 6 weeks

Implantation of drug eluting stent within 12 months

Recent cerebral infarct within 6 months

Heparin induced thrombocytopenia

Heparin resistance

Menstruation

No approval of study

Preoperative use of cardiopulmonary bypass, continuous veno-venous hemofiltration, or intraarotic balloon pump

Continuous use of other anticoagulants except aspirin such as plavix, heparin, low molecular weight heparin until operating day

**Criteria of drop-out**

Declaration of approval

Intraoperative use of cardiopulmonary bypass, continuous veno-venous hemofiltration, or intra-aortic balloon pump

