**Randomization**

All subjects will be randomly assigned with 1:1 ratio to two groups as following:

- Control group: patients receiving low dose aspirin (100 mg/day) until operating day
- Study group: patients stop aspirin (100 mg/day) 4 days before surgery

Random sequence will be made by a study nurse with size 2 blocks (AA, AB, BA, BB) including letter of ‘A’ (meaning aspirin continuation group) and ‘B’ (meaning aspirin discontinuation group). And then each generated letter will be concealed in an envelope in the order of generation. Enrolled patients will be allocated to their groups depending on the letter (A or B) inside the concealed envelopes that will be opened by an anesthesiologist who was unaware of the study.

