**Study protocol**

Assigned ward nurses will deliver drugs to all patients during the perioperative period.

In the aspirin continuation group (n=24), aspirin (100 mg; aspirin protect®, Bayer AG, Leverkusen, Germany) will be administered every morning until the operative day.

In the aspirin discontinuation group (n=24), aspirin will be stopped 4 days before the operative day.

Other anticoagulants, such as clopidogrel or warfarin will be stopped at least 5 days before surgery in all patients.

Anesthetic and surgical techniques will be standardized during the trial. A single anesthesiologist and a single surgeon, not aware of the group assignment, will perform OPCAB in all patients. All patients will arrive in the operating room without premedication. A catheter will be inserted at radial artery after local anesthesia for continuous arterial blood pressure monitoring. And standard monitoring including ECG, NIBP, SpO_2_ and BIS monitoring. Anesthesia will be induced with 0.15 mg/kg midazolam, 1-2 μg/kg sufentanil and vecuronium. After endotracheal intubation, mechanical ventilation will be applied to maintain an end-tidal carbon dioxide tension of 35-40 mmHg. Anesthesia will be provided with target-controlled infusion of propofol and remifentanil.

Target activated clotting time (ACT) will be 250-350 s.

1.5 mg/kg unfractionated heparin will be administrated before making of Y-graft.

At following time points, blood will be sampled for evaluation of platelet activation and responsibility.

- T1. Before skin incision
- T2. After reperfusion of graft
- T3. End of surgery
- T4. 24 h postoperatively
- T5. 48 h postoperatively
- T6. 72 h postoperatively
- T7. 96 h postoperatively

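### Dropping randomised patients for bypass, hemofiltration or balloon pump during surgery contradicts the stated intention-to-treat analysis

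*Protocol*

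**What the plan says.** The protocol's Statistical analyses section states: "Statistical analyses will be performed with intention-to-treat". It does not define that set further.

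Criteria of drop-out has two entries. One reads "Declaration of approval", which I take to mean withdrawal of consent and do not dispute. The other is "Intraoperative use of cardiopulmonary bypass, continuous veno-venous hemofiltration, or intra-aortic balloon pump".

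On timing, the Randomization section defines the discontinuation arm as "Study group: patients stop aspirin (100 mg/day) 4 days before surgery".

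Number of subjects states that "20 subjects are needed for each group, that is, total of 40 subjects are needed for this study", then adds a 20% loss rate to reach 48, which is 24 per arm. No section says that a patient who meets a drop-out criterion stays under follow-up, gives the later mRNA sample or is kept in the analysis.

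**The concern.** Intention-to-treat means that every randomised patient is compared in the arm to which he or she was allocated, whatever happens afterwards. A drop-out rule triggered by an event in the operating room takes patients out after randomisation and after the two aspirin strategies have had time to act.

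This matters if the event is related both to the arm and to the outcome. The Background gives grounds for both links:

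- **Arm to event.** It associates aspirin with reduced platelet function and a greater bleeding tendency under bypass, and platelet dysfunction with thrombosis or bleeding around surgery. The aspirin strategy could therefore affect who needs support.
- **Event to outcome.** It reports more abnormal platelet function after operations with bypass. Patients converted to bypass may therefore differ on GPIIb mRNA and the other platelet measures.

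If both links hold, the patients who remain are no longer a randomised comparison. Bleeding volume and MACE are also listed outcomes, and with 24 patients per arm a few removals could change how they look.

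**Working it through.** **Order of events**

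1. Allocation must come at least 4 days before surgery, because one arm stops aspirin then (Randomization; Study protocol).
2. The baseline sample T1 is taken before skin incision (Study protocol).
3. The drop-out event occurs during surgery (Criteria of drop-out).
4. The second mRNA sample, T6, is taken days after surgery (Laboratory evaluation lists).

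The event thus falls after randomisation, after the arms diverge and after baseline, but before the primary outcome is measured.

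**The loss allowance**

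- The plan's figure is reproduced by 40 × 1.20 = 48.
- The allowance is 48 − 40 = 8 patients, or 8/48 = 16.7% of those randomised.
- Dividing by the retained fraction would give 40/0.80 = 50, and a 20% loss from 48 leaves 48 × 0.80 = 38.4. This is a minor side point.
- What matters here is that the 40 are patients remaining after loss, so the plan treats lost patients as not contributing.
- The base figure of 20 per group cannot be reproduced, because no difference, SD or power is given.

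**Possible bias (assumed inputs, none from the protocol)**

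Let r1 and r2 be the proportions removed in the two arms, and let removed patients lie s SD above those retained in the same arm. The mean of all patients in an arm equals the mean of those retained plus r × s. The difference among retained patients is therefore off by (r2 − r1) × s.

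| Removed, arm 1 vs arm 2 | s = 0.5 | s = 1.0 | s = 1.5 |
|---|---|---|---|
| 10% vs 10% | 0 | 0 | 0 |
| 5% vs 15% | 0.05 SD | 0.10 SD | 0.15 SD |
| 0% vs 20% | 0.10 SD | 0.20 SD | 0.30 SD |

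If all 8 allowed losses were device-related and split 6 to 2, with s = 1, the error would be (6/24 − 2/24) × 1 = 0.17 SD.

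The zero row assumes the same s in both arms. If s differs, the error is r2 × s2 − r1 × s1, and equal removal rates alone do not guarantee zero.

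**Scale**

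With 20 per arm:

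- The standard error of the difference is √(2/20) = 0.32 SD.
- The difference detectable with 80% power at two-sided 0.05 (normal approximation) is (1.960 + 0.842) × 0.316 = 0.89 SD.
- For 90% power it is (1.960 + 1.282) × 0.316 = 1.03 SD.

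**The case against.** **Removal is inferred.** The drop-out section does not say whether drop-out ends procedures, follow-up or inclusion in the analysis, and analysis sets are often defined in a SAP. This is true as far as it goes. But the loss allowance points to removal and nothing points to retention. If retention is intended, the protocol still has to say so.

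**The bias may be small.** A 6-to-2 split uses the whole allowance, which must also cover withdrawals and missing samples. It puts 25% device use in one arm of an elective, first-surgery population that excludes recent MI, unstable angina and PCI. Even then, 0.17 SD is about half a standard error. This stands, and the figures are illustrations only.

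**Blinding.** The single surgeon and anesthesiologist do not know the assignment, so knowledge of the arm should not drive conversion. This also stands, but it does not remove an effect of aspirin itself on bleeding or ischaemia.

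**An off-pump population is a reasonable interest.** Bypass itself disturbs platelets, and a few exposed patients could distort a mean percent change compared by t-test. A modified intention-to-treat analysis could be defended under that label. That is not the label the plan uses, and such a set would still be selected on an event after randomisation. A sensitivity analysis answers the same question.

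**Stronger readings the text does not support.** A reader might infer that exclusions reaching up to surgery, such as "Preoperative use of cardiopulmonary bypass, continuous veno-venous hemofiltration, or intraarotic balloon pump" or "Continuous use of other anticoagulants except aspirin such as plavix, heparin, low molecular weight heparin until operating day", are also applied after allocation. The protocol does not say so. Randomization allocates patients already enrolled, and Study protocol has "Other anticoagulants, such as clopidogrel or warfarin will be stopped at least 5 days before surgery in all patients", so that criterion can be settled before the arms diverge. A reader might also infer that bleeding and MACE cluster in the dropped patients and vanish from the results. The protocol gives no conversion or event rates and does not say that clinical outcomes go uncollected in drop-outs.

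**Conclusion.** The contradiction is in the text: a rule that drops patients for an event during surgery cannot stand beside an unqualified intention-to-treat statement. It bears on the primary comparison, and it needs settling before patients are operated on, because a postoperative sample that was not taken cannot be recovered.

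That this biases the result is possible, not shown. It requires the device events to depend on the arm and to be related to outcome. The Background makes both plausible, but the protocol quantifies neither. The bias is 0 if losses are equal and unrelated to outcome, and about 0.05 to 0.30 SD under the assumed lopsided losses. That upper end is roughly one standard error and about a third of the difference detectable with 80% power (0.30/0.89 = 0.34). Its direction cannot be derived. Confidence is high for the contradiction and does not extend to the size of the bias.

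**What to change.** 1. Remove the intraoperative device criterion from Criteria of drop-out and record such use as a protocol deviation.
2. State that the intention-to-treat set is all randomised patients, analysed in their allocated arm.
3. In patients with intraoperative bypass, hemofiltration or balloon pump, take the primary-outcome mRNA sample and collect the clinical outcomes as for everyone else. Their T1 baseline already exists, since it precedes incision.
4. Report the analysis excluding converted patients as a labelled sensitivity analysis.

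The sample time must be clear for step 3. Study protocol places T6 at 72 h while Primary Outcomes labels it 96 h, and these two passages have to be reconciled.

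The cost is wording, one further mRNA assay set for each affected patient, and some added variance from bypass-exposed patients. With about 20 per arm that variance may not be negligible, which is why the sensitivity analysis should be reported alongside.
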